### Intervention

3.8

We will propose the standard procedures for shunt implantation and surgeons will be trained before recruitment. We will utilize the shunt system with programmable pressure valve, which will be set to its highest level before surgery.^[14]^ After shunt insertion, the pressure setting will be lowered by 1-level according to the symptoms or radiological signs.^[15]^

### Ventriculoperitoneal shunt

3.9

VPS will be performed under general anesthesia and the proximal shunt tubing will be inserted into the right lateral ventricles. A ventricular catheter is inserted into the lateral ventricle. The valve will be placed at the cranial incision with a 3-point fixation to the subcutaneous tissue. A subcutaneous tunneler is made to connect the valve with abdominal cavity. The peritoneal catheter will be inserted if the CSF flow through shunt catheter is observed.

### Lumboperitoneal shun

3.10

The patients in the left lateral position under general anesthesia. A lumbar catheter is inserted through the L3/4 interlaminar space into the spinal subarachnoid space. A subcutaneous flank region is then made to fix the valve. A subcutaneous tunneler is made to connect the spinal subarachnoid space, frank region, and abdominal cavity. The peritoneal catheter will be inserted if the CSF flow through shunt catheter is observed.

### Outcomes

3.11

Evaluation schedule is shown in Fig. 1. Each participant is evaluated before surgery, 1 month, 12 months, and 5 years after surgery by 2 independent assessors.

**Figure 1 F1:**
[figure not shown]
The schedule of enrolment, interventions, and assessments. # The position of MRI scan include brain, lumbar, and abdomen. ∗ “Shunt outcome” includes shunt failure and shunt success. INPHGS = idiopathic normal pressure hydrocephalus grading scale, LPS = lumboperitoneal shunt, MMSE = Mini-Mental State Examination, MRI = magnetic resonance imaging, mRS = modified Rankin Scale, VPS = ventriculoperitoneal shunt.

**Figure 2 F2:**
[figure not shown]
The flow chart of the selection pf patients. CSF = cerebrospinal fluid, INPHGS = idiopathic normal pressure hydrocephalus grading scale, LPS = lumboperitoneal shunt, MMSE = Mini-Mental State Examination, mRS = modified Rankin Scale, VPS = ventriculoperitoneal shunt.

### Primary outcome

3.12

The primary outcome is the rate of shunt failure within 5 years. According to previous studies, shunt failure is defined as the presence of shunt obstruction, breakage, exposure, misconnection, infection, or any conditions requiring shunt revision. Shunt success is defined as improvement without shunt revision.^[16]^

### Secondary outcomes

3.13

The secondary outcomes include mRS, INPHGS, MMSE, and Evans index at 1 month, 12 months, and 5 years after surgery. We will calculate the rate of favorable outcome, which is defined as shunt success and an improvement of more than 1 point in the mRS at evaluation point. Evans index is tested thorough magnetic resonance imaging scan. We will also analyze the complications throughout the study within 5 years after shunt insertion.

Safety indicators include any serious adverse event, which is defined as death, consciousness disorders, admission to intensive care unit, deterioration, or an extension of the length of stay, or disability, which is associated with shunt surgery.^[17]^

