### Randomizing and blinding

3.7

This trial is randomized and open-label. We will complete the randomization through a random number table, but the data collectors, accessors, and analysts are blinded to allocation.

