### Data monitoring

3.16

An independent data monitoring committee (DMC) consisting of neurologists, assessors, and data analysts from West China Hospital will check the data once a year to guarantee the efficacy and safety and of this trial.

All adverse events will be recorded in detail, properly handled and tracked until they were properly resolved or stable, and be timely reported to ethics committee and competent department. We will conduct cumulative review on all adverse events on a regular basis, and convene a meeting of researchers to assess the risk of the study if necessary.

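### The serious adverse event definition ties seriousness to relatedness and omits new hospital admission, so the comparison of serious events and deaths between arms rests on a causality judgement

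*Protocol article*

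**What the plan says.** The Secondary outcomes section (3.13) of the protocol article sets the safety measure: "Safety indicators include any serious adverse event, which is defined as death, consciousness disorders, admission to intensive care unit, deterioration". The list continues with "or an extension of the length of stay, or disability, which is associated with shunt surgery". Prolongation of a stay is included; a new admission is not.

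The same section adds a second safety analysis: "We will also analyze the complications throughout the study within 5 years after shunt insertion".

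The Data monitoring section (3.16) states that "All adverse events will be recorded in detail, properly handled and tracked until they were properly resolved or stable", and also "We will conduct cumulative review on all adverse events on a regular basis". Neither statement is restricted to related events.

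On blinding, the Randomizing and blinding section (3.7) states "This trial is randomized and open-label", then qualifies this: "but the data collectors, accessors, and analysts are blinded to allocation". The article does not name the person who decides whether an event is associated with surgery.

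**The concern.** Seriousness and relatedness are separate attributes of an adverse event. Seriousness describes what happened to the patient; relatedness is an opinion about why. When the second is a condition of the first, events judged unrelated leave the serious count.

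Randomisation supports comparing all events between arms. It does not protect a comparison of the subset that remains after a judgement made once the operation is known or could be guessed. If the same kind of event is attributed to surgery more readily after one operation than after the other, the arms will differ in their counts even when the patients fared equally. Safety is part of the objective stated in section 2, so this comparison matters.

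The missing admission item is a smaller, separate defect. Follow-up lasts 5 years, and most hospital contact after the first discharge will take the form of a new admission rather than a longer stay.

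**Working it through.** **1. How far the closing clause reaches.** The list is "defined as death, consciousness disorders, admission to intensive care unit, deterioration, or an extension of the length of stay, or disability", followed directly by the relatedness clause.
- If the clause governs the whole list, every item, including death, needs a link to surgery. This is the likelier reading, since a rule that filters only the last item would be odd.
- If it governs only the last item, all deaths count and the filter applies to disability alone.

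Two careful readers could therefore produce different counts from the same data.

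**2. What other sections already cover.**

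| Kind of event | Where it is covered |
|---|---|
| Listed shunt faults, infection, any condition needing revision | Primary outcome over 5 years (3.12) |
| Other complications to 5 years | Separate analysis (3.13), no seriousness threshold |
| Any adverse event | Recorded, followed up and cumulatively reviewed (3.16) |
| Listed serious event judged unrelated, including death | Recorded, but outside the serious event count on the likelier reading |
| New admission that meets no other listed criterion | Recorded, but not counted as serious |

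The last two rows are the gap. The follow-up items named in section 3.14 include complications and serious adverse events but not all-cause death, and no stated endpoint clearly compares it by arm.

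**3. What differential attribution could do.** The protocol gives no rate of serious events and no attribution rate, so there is no figure of its own to reproduce. This is an illustration on assumed inputs. Only the 300 per arm (section 3.6) and the 5% significance threshold (section 3.15, taken as two-sided) come from the document.

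Let the true all-cause rate p be the same in both arms, and let shares q1 and q2 be attributed to surgery. The counted rates are p1 = p·q1 and p2 = p·q2, with mean m. The chance of a significant result in the direction of the larger share is approximately

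Φ[(|p1 − p2| − 1.96·se0) / se1], where se0 = √(2m(1 − m)/300) and se1 = √((p1(1 − p1) + p2(1 − p2))/300).

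Worked case, p = 0.20, q1 = 0.5, q2 = 0.6: p1 = 0.10, p2 = 0.12, m = 0.11, se0 = 0.02555, se1 = 0.02553. The argument is (0.02 − 1.96 × 0.02555)/0.02553 = −1.18, so the chance is about 0.12.

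| True rate p | 50% v 50% | 50% v 60% | 40% v 60% |
|---|---|---|---|
| 10% | 2.5% | 8% | 20% |
| 20% | 2.5% | 12% | 37% |
| 30% | 2.5% | 17% | 54% |
| 40% | 2.5% | 22% | 69% |

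With equal shares there is no inflation, only a smaller count. Bias needs attribution to differ by arm.

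**4. How many deaths would be subject to attribution.** Assume a constant annual mortality hazard μ of 0.03 to 0.08. Deaths by 5 years are 1 − exp(−5μ): 13.9% at 0.03 and 33.0% at 0.08. Of 600 patients that is about 84 to 198. This is the number of deaths to be classified. It does not measure misclassification or bias.

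**The case against.** The best defence is that the trial has several layers of safety capture. Shunt faults and revisions are in the primary outcome, complications are analysed to 5 years whatever their severity, and every adverse event is recorded and reviewed. The text says that safety indicators include serious events, which is not a limit to them. A readmission for a shunt complication would fall under the complications analysis and perhaps under the primary outcome, and might meet the undefined item of deterioration. An article may also leave the choice of adjudicator to the full protocol. Most of this stands, and it narrows the point. It does not answer the point that the definition itself, as printed, makes cause part of seriousness and leaves out new admission.

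Three stronger readings are tempting, and the documents do not support them:
- *Unblinded attribution decides the safety comparison.* A reader might infer this from the open-label label and the two different operations. But section 3.7 blinds data collectors and assessors, section 3.14 has data collectors record the serious events, no judge of association is named, and complications are a separate safety analysis.
- *Most late harm may be missed.* Sections 3.12, 3.13 and 3.16 together contradict this.
- *The yearly safety review sees less.* Section 3.16 has the monitoring committee check the data yearly without any limit to related events, and provides for cumulative review of all adverse events.

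**Conclusion.** The point holds in a limited form. The definition mixes seriousness with relatedness, its closing clause is ambiguous, and new hospital admission is absent. On the likelier reading, the between-arm comparison of serious events and deaths depends on a post-randomisation causality judgement in an open-label trial. What can drop out is confined to events judged unrelated and to admissions that meet no other listed criterion.

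The size cannot be taken from the documents. Under the assumed rates above, a 10-point difference in attribution gives a chance of about 8–22% of a spurious significant difference in one direction, and a 20-point difference about 20–69%, against a nominal 2.5%. The documents do not show that attribution would differ; they leave the comparison exposed if it does. If the clause limits only disability, deaths already count and most of the relatedness concern falls away, but the sentence still needs rewording and the admission item is still missing.

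**What to change.** Reword the definition in section 3.13 so that an event is serious irrespective of cause, and add new or prolonged hospital admission to the list. Record relatedness to surgery in a separate field, judged without knowledge of the arm where that is feasible. State that all-cause serious events and all-cause death are compared by arm first, with related events in a secondary table.

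The cost is a change of wording, one extra data field, and more events to classify and report. Since section 3.16 already has all adverse events recorded, little new data collection is needed.

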### Data collection and management

3.14

Two independent data collectors will collect the baseline information (age, sex, comorbidities, recruitment time, CSF opening pressure, clinical manifestations, radiological features) at the time of admission, perioperative conditions, and follow-up outcomes at each evaluation point (shunting outcomes, mRS, INPHGS, MMSE, Evans index, complications, serious adverse events). The data is first recorded in paper and then stored in Excel.

### Statistics analysis

3.15

We will use SPSS 19.0 software to analyze the data. The statistical description of categorical variables adopts number (percentage). For continuous data, firstly, the Kolmogorov Smirnov test will be used to analyze the normality. The statistical description in accordance with the normal distribution is mean ± standard deviation (SD), and the median (range) description is used for those do not follow the normal distribution. Wilcoxon rank sum test or *t* test is used to compare the difference of continuous data according to the normality. Chi-Squared test is used to compare the difference of categorical variables. Kaplan–Meier survival analysis is used to draw the shunt-success curve. In this study, *P* value under .05 is considered to be statistically significant.

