### Sample size

3.6

A recent meta-analysis systematically reviewed the shunting outcomes in patients with INPH and showed the rate of VPS failure and LPS failure were 18.0% and 14.0%, respectively.^[13]^ Therefore, a sample of 250 for each group will be required in this trial with a significance level of 5% (two-sided) and a power of 80% to demonstrate a 20% difference. Finally, the sample size will be enlarged to 300 for each group.

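### Continuous secondary outcomes are compared without baseline adjustment, by a test chosen from a normality pre-test, although participants are evaluated before surgery

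*Protocol article*

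**What the plan says.** Section 3.13 of the protocol article defines the outcomes concerned: "The secondary outcomes include mRS, INPHGS, MMSE, and Evans index at 1 month, 12 months, and 5 years after surgery". Section 3.11 adds a pre-operative assessment on the same schedule: "Each participant is evaluated before surgery, 1 month, 12 months, and 5 years after surgery by 2 independent assessors". Section 3.2 gives the same four time points.

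Section 3.15 fixes the analysis. For continuous data, "the Kolmogorov Smirnov test will be used to analyze the normality" as the first step. The result decides two things: whether the summary is mean and SD or median and range, and whether a t test or a rank-sum test "is used to compare the difference of continuous data according to the normality". For the rest, "Chi-Squared test is used to compare the difference of categorical variables". Kaplan-Meier is kept for the shunt-success curve. The section names no covariate, change score or repeated-measures model.

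The only outcome definition that uses a baseline value is the binary favorable outcome in section 3.13: "shunt success and an improvement of more than 1 point in the mRS at evaluation point".

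**The concern.** When a scale is measured before and after surgery, the pre-operative value usually explains part of the spread at follow-up. A comparison of follow-up values alone leaves that part in the error term. The trial bears the cost of the pre-operative evaluation, but the stated comparisons of the scales do not use it.

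The pre-test adds a separate difficulty. The t test concerns a difference in means. The rank-sum test concerns whether values in one group tend to exceed those in the other. Letting the data choose between them means the question is not settled in advance. One scale could be reported as means with a t test at 12 months and as medians with a rank-sum test at 5 years, which makes its course over time hard to read.

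At stake are the precision and readability of the functional, cognitive and imaging results. The primary outcome is not affected.

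**Working it through.** **The plan's own figure.** The article gives no power or precision figure for the secondary outcomes, so there is none to reproduce. Its only design figure, 250 per group enlarged to 300 (section 3.6), is for shunt failure. The standard two-proportion formula does not return 250 for 18.0% against 14.0%; it gives 1318 per arm. That is a separate matter, and only the 300 per arm is used below.

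**Inputs.** n = 300 per arm with complete follow-up; two-sided 5% level and 80% power, borrowed from section 3.6; equal allocation. The correlation ρ between a scale's pre-operative and follow-up values is not in the documents and is assumed at 0.3, 0.5 and 0.7.

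**Formulas**, with the outcome in SD units:

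- Variance of the group difference: unadjusted 2/n; ANCOVA (1 − ρ²) × 2/n.
- Smallest effect detectable with 80% power, unadjusted: (1.960 + 0.842) × √(2/300) = 2.802 × 0.0816 = 0.229 SD.
- The same with ANCOVA: 0.229 × √(1 − ρ²).
- ANCOVA power at 0.229 SD: Φ(2.802/√(1 − ρ²) − 1.960). For ρ = 0.5 this is Φ(2.802/0.866 − 1.960) = Φ(1.275) = 89.9%.
- Patients per arm for the precision of 300 unadjusted: 300 × (1 − ρ²).

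| Assumed ρ | 1 − ρ² | Variance cut | Detectable effect (SD) | Power at 0.229 SD | Equivalent n per arm |
|---|---|---|---|---|---|
| Unadjusted | 1 | none | 0.229 | 80.0% | 300 |
| 0.3 | 0.91 | 9% | 0.218 | 83.6% | 273 |
| 0.5 | 0.75 | 25% | 0.198 | 89.9% | 225 |
| 0.7 | 0.51 | 49% | 0.163 | 97.5% | 153 |

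The proportional variance cut does not depend on n, so it also applies if fewer patients are seen at 5 years.

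**If change from baseline were meant.** Section 3.15 does not say so. Its variance factor would be 2(1 − ρ): 1.4, 1.0 and 0.6 at the three correlations. Each exceeds the ANCOVA factor (0.91, 0.75, 0.51), and at ρ = 0.3 it is worse than no adjustment.

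**The procedure as written.** A simulation used an MMSE-like integer score (0 to 30, assumed mean 22, SD 5), 300 per arm and 1000 runs per setting. Each arm was pre-tested with the Lilliefors-corrected Kolmogorov-Smirnov test, and the rank-sum test was used if either arm rejected normality.

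| ρ | Type I error, as written | Type I error, ANCOVA | Power, as written | Power, ANCOVA |
|---|---|---|---|---|
| 0.3 | 4.8% | 5.3% | 77.4% | 83.8% |
| 0.5 | 5.1% | 5.0% | 77.8% | 90.2% |
| 0.7 | 4.1% | 4.3% | 77.9% | 97.5% |

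The simulated ANCOVA powers agree with the formula. The two-step procedure gains nothing as ρ rises.

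**Stability of the pre-test.** In 400 runs at n = 300, the same MMSE-like score was declared non-normal in 96.5% of runs with the Lilliefors correction and 19.5% without it. An Evans-like index (assumed mean 0.36, SD 0.04) rounded to two decimals gave 99% and 24%; unrounded it gave 4.5% and 0%. These distributions are assumed. They show that the choice of test can turn on rounding and on which version of the test is run, neither of which section 3.15 states.

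**The case against.** The strongest reply is that nothing stated is invalid. Under randomization both tests hold their level, and the simulation bears this out. A reader might infer that leaving out baseline biases the comparison through chance imbalance. It does not, because the error rate already allows for that. This part of the reply stands in full: the loss is one of precision.

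A second reply is that a condensed article leaves covariates and models to an analysis plan. That would answer silence, but section 3.15 is not silent. It names a particular procedure, which a later plan would have to contradict. The reply does succeed against one stronger reading, that the trial will report P values with no effect estimate or interval. Section 3.15 names tests and summaries and does not rule out estimates.

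Other stronger readings also fail:

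- *That all four scales go to the t or rank-sum test.* Section 3.15 does not classify mRS or INPHGS. Either could go to the chi-squared test, which is also unadjusted.
- *That the pre-test must reject normality on these scales.* One value held by a share h of patients forces a Kolmogorov-Smirnov distance of at least h/2. With the uncorrected critical value 1.36/√n, rejection is certain only above 15.7% at n = 300 or 11.1% at n = 600. Seven mRS levels guarantee only 1/7 = 14.3% in some level. That suffices if the arms are pooled but not within one arm, and the article does not say which is tested. For MMSE the result depends on the version of the test, and Evans index is a measured ratio.
- *That baseline data are discarded.* Baseline mRS enters the favorable outcome.

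Finally, the gain depends on ρ, and at 0.3 it is small. That stands, which is why the range is shown.

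**Conclusion.** The point holds as an efficiency and pre-specification weakness in section 3.15. It is firm for MMSE and Evans index and conditional for INPHGS and mRS, whose handling is not stated. The variance given up is 9% to 49% for assumed correlations of 0.3 to 0.7. At 300 per arm this is the difference between 80% power and about 84% to 97.5% for the same effect. These figures assume complete follow-up and a roughly linear relation between baseline and follow-up values, and they describe ANCOVA against a comparison of means. The data-driven choice of test and summary is a defect whatever the correlation. Because type I error is sound and these outcomes are secondary, the change is worth making but does not threaten the trial's validity.

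**What to change.** In section 3.15, remove the normality-driven choice for the secondary outcome comparisons and pre-specify, at 1 month, 12 months and 5 years:

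- **MMSE, INPHGS and Evans index:** ANCOVA adjusted for the same scale's pre-operative value, reporting the adjusted mean difference (LPS minus VPS) with its 95% CI.
- **mRS:** an ordinal (proportional-odds) model adjusted for baseline mRS, reporting the common odds ratio with its 95% CI.

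Fix one descriptive summary per scale and use it at every visit. The baseline list in section 3.14 does not name the four scales, so state there that their pre-operative values are recorded.

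The cost is wording only. The pre-operative evaluation is already scheduled, Evans index is needed for eligibility (section 3.4), and the favorable outcome already needs baseline mRS. These models are available in standard software.

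### The only named test that fits the five-year failure rate is chi-squared, which cannot handle patients lost before five years; Kaplan–Meier only draws a curve, and of a different outcome

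*Protocol article*

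**What the plan says.** All references are to the protocol article.

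- Primary outcome (3.12): "The primary outcome is the rate of shunt failure within 5 years". Failure is defined there: "shunt failure is defined as the presence of shunt obstruction, breakage, exposure, misconnection, infection, or any conditions requiring shunt revision". So is success: "Shunt success is defined as improvement without shunt revision".
- Statistics analysis (3.15): a t test or Wilcoxon test for continuous data, then "Chi-Squared test is used to compare the difference of categorical variables", then "Kaplan–Meier survival analysis is used to draw the shunt-success curve". No between-group test or estimate is attached to the curve.
- Outcomes (3.11): "Each participant is evaluated before surgery, 1 month, 12 months, and 5 years after surgery by 2 independent assessors".
- Sample size (3.6) plans on two proportions: "the rate of VPS failure and LPS failure were 18.0% and 14.0%, respectively".
- Death appears only under the safety indicators in 3.13. The introduction calls the condition a geriatric disorder, and 3.1 lets participants withdraw at any stage. No death or loss rate is given.

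**The concern.** Shunt failure accrues over five years. A chi-squared test on crude proportions needs a five-year status for every patient. A patient who withdraws or is lost in year two without a failure has none, so the analyst must either call that patient a non-failure or drop the patient. The two choices push the estimated rate in opposite directions, and neither uses the two event-free years correctly.

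The article does name a method suited to incomplete follow-up, but gives it only the job of drawing a curve. That curve also shows a different outcome. A patient who never needs a revision and never improves is not a success, yet is not a shunt failure either, so one minus the success curve is not the primary outcome.

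What is at stake is the accuracy of the failure rate in each arm and, if loss differs between arms, the validity of the comparison.

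**Working it through.** **Inputs.** From Sample size (3.6): failure 18% (ventriculoperitoneal) and 14% (lumboperitoneal), and 300 patients per arm. Assumed, because the article gives none: constant hazards acting independently, death (μ) at 3, 5 or 8% a year, and loss (c) at 3% a year unless stated. The article has no figure of its own on this point to reproduce.

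**1. Level of the failure rate in one arm.** Net failure of 18% at five years gives λ = −ln(0.82)/5 = 0.0397 a year.

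- Target, cumulative incidence with death as a competing event: λ/(λ+μ) × [1 − exp(−5(λ+μ))].
- Lost and dead counted as non-failures: O = λ/(λ+μ+c) × [1 − exp(−5(λ+μ+c))].
- Lost and dead dropped, observed failures kept: O/(O + C), where C = exp(−5(λ+μ+c)).

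| Death a year | Cumulative incidence | Counted as non-failures | Dropped |
|---|---|---|---|
| 3% | 16.8% | 15.6% | 20.5% |
| 5% | 16.0% | 14.9% | 21.4% |
| 8% | 14.9% | 14.0% | 22.8% |

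Kaplan–Meier with death censored returns the net 18% in every row, so it also overstates the cumulative incidence.

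**2. Which part is due to death.** Setting c = 0 makes O identical to the cumulative incidence: 16.8, 16.0 and 14.9%. Counting deaths as non-failures therefore causes no distortion for this target. The drop from the second column to the third comes entirely from loss. Deaths distort only when they are excluded or censored.

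**3. Between-arm difference, equal death/loss.** True rates are 18% and 14%, a difference of 4.0 points. Five-year death/loss is set at L, with hazard −ln(1−L)/5, in both arms.

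| L | Difference, counted as non-failures | Difference, dropped |
|---|---|---|
| 10% | 3.8 | 4.2 |
| 20% | 3.6 | 4.3 |
| 30% | 3.4 | 4.5 |
| 40% | 3.2 | 4.8 |

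With identical arms and equal loss, the chi-squared test keeps its 5% level.

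**4. Unequal loss, identical true failure of 18%.** Loss of 2% versus 6% a year is 1 − exp(−0.10) = 9.5% versus 1 − exp(−0.30) = 25.9% over five years.

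| Death a year | Counted as non-failures | False difference | Dropped | False difference |
|---|---|---|---|---|
| 3% | 16.0 vs 14.6% | 1.4 points | 20.0 vs 21.8% | 1.8 points |
| 5% | 15.3 vs 14.0% | 1.3 points | 20.9 vs 22.8% | 1.9 points |
| 8% | 14.3 vs 13.1% | 1.2 points | 22.3 vs 24.3% | 2.0 points |

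The two counting rules err in opposite directions. With 300 randomised per arm, the false-positive rate at nominal 5% is 7.1–7.6% under either rule. More extreme combined death/loss does more harm. Counting these patients as non-failures, 20% versus 40% over five years gives 2.0 points and 10.4%; 10% versus 40% gives 2.9 points and 16.4%.

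**5. Power.** The hazard ratio is ln(0.86)/ln(0.82) = 0.76. With 300 per arm and no loss, 300 × (0.18 + 0.14) = 96 failures are expected. Log-rank power is Φ(0.2744 × √(96/4) − 1.96) = 26.9%, against 26.6% for chi-squared. With 20% death/loss the figures are 24.7% and 24.2%; with 40%, 22.2% and 21.6%.

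**The case against.** The strongest reply is that 3.15 is a general list and assigns no test to any endpoint. A fuller analysis plan could name a log-rank test or a rule for deaths and losses, and an article commonly leaves such detail out. This stands in part: the link from chi-squared to the primary outcome is an inference. It is the natural one, since no other named test fits a failure rate and 3.6 plans on two proportions. The point also rests on what is printed, namely a survival method given only a graph, of an outcome other than the primary one.

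Four stronger readings are tempting, and the documents do not support them.

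- *Deaths necessarily distort the comparison.* They do so only if excluded or censored, and no section says that they will be.
- *The counting rule matters more than the 4-point planning difference.* The 14.0–22.8% spread is a shift in the level of one arm under different rules. The 4 points are a difference between arms, and one rule would apply to both. With equal loss that difference stays within about 3.2–4.8 points.
- *A spurious result is likely.* Unequal loss is an assumption. Nothing in this 1:1 randomised, single-centre design points to a threefold imbalance.
- *Event times between month 12 and year 5 will be missing.* A Kaplan–Meier curve presupposes event times. Complications are analysed over the full five years (3.13), adverse events are recorded and tracked, and data are checked yearly (3.16). The dates may largely exist; the article just does not tie them to the primary analysis.

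**Conclusion.** The concern holds in a moderate form. As printed, the analysis fits the primary outcome poorly: the one applicable test cannot accommodate patients lost before five years, and the survival curve describes something other than shunt failure.

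Under the assumed rates, each arm's failure rate would be understated by about 1 point (losses counted as non-failures) or overstated by about 4 to 8 points (lost and dead dropped). The comparison is more robust: essentially unaffected in test level under equal loss, and at about 7–8% false positives under a threefold imbalance in loss. These sizes rest on assumed death and loss rates, constant independent hazards, and the inference that chi-squared is meant for the primary outcome.

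The change is worth making for a sound estimate and protection against unequal follow-up. It is not a remedy for power. The stated 250 per group does not follow from 18% versus 14%, which needs 1,318 per group at two-sided 5% and 80% power; that is a separate problem.

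**What to change.** In section 3.15:

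- Make the primary comparison time from surgery to first shunt failure, in all patients as randomised, with loss censored and death treated as a competing event.
- Report five-year cumulative incidence per arm and the difference with a 95% confidence interval.
- Name one between-group time-to-event test, either Gray's test or a cause-specific log-rank test. Promoting Kaplan–Meier with death censored as the estimate of the failure rate would not do, because it overstates failure.
- Keep chi-squared as a sensitivity analysis, with a stated rule for patients who die or are lost.
- Plot time to shunt failure instead of shunt success.

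Record three dates: failure or revision, death, and last contact. The existing visits, adverse-event tracking and yearly data check can carry these, so no added patient contacts are required.

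**Cost.** A change of wording, three date fields, and possibly software other than SPSS 19 for the competing-risk analysis.
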